### Sample size and power calculations

The assumptions for the power calculations were that patients aged 65 and over represent 17% of the total population; that 40% of study population will be in the high risk group.

Also assuming that:

1. Minimum worthwhile change in detection rate was 1% for targeted screening versus routine practice. It is estimated that this change would equate to £10,000 per life year gained. This is based on the following assumptions:

a) 60% of new cases of identified AF would be suitable candidates for warfarin

b) Annual risk of stroke in this population was 5%, reduced by 60% to 2% if treated

c) Costs: £25 to screen a patient; £100 to treat with warfarin pa; £6,000 NHS costs to treat a stroke

2. 50% of patients with AF will be already known to their general practitioner (estimates range from 30% [19] to 76% [20])

3. Community prevalence of AF in this population was 6% [2]

See figure 1. It was assumed that the baseline prevalence of AF known to the practice (A1) would be 3% (i.e. half of real prevalence of 6%) and that the prevalence of known AF in the control practices would remain constant over the screening period. Thus, the change in the prevalence of known AF in the control practices between baseline to follow up (C2-C1) should be approximately 0%. The change in the GP educated arm (B2-A1) should be marginally higher and is assumed to be between 0 and 1%. The change in the systematic screening arm should, on average, be between 0 and 3% and was assumed to be approximately 2% for the total screening arm (A3-A1) and in the high risk arm (A2-A1) was approximately 3%.

All sample size calculations were for 90% power and 5% significance levels unless otherwise stated.

*a) To detect a 1% difference in detection rate between intervention (GP educated) and control practices (B2-A1) vs (C2-C1). *This requires 1,236 patients. However, since this is a difference based at the practice level of randomisation, it needed to be inflated by the design factor. Based on AF prevalence data from the EcHoES (Echocardiographic Heart of England Screening) Study [2], the between practice variance is 3.7 and the within practice variance is 246. This gave an intra-cluster correlation coefficient of 0.015. The most efficient design in this circumstance would be a cluster size of 200, which gives a design factor of 4. Therefore, 5,000 patients would be needed in 25 practices in both intervention (GP educated) and control groups.

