*f) To detect a relative risk (RR) of 2 (1% detection rate difference) between total population and high risk screening (A3 vs A2).*It was assumed that 40% of the study population fall into the high risk group, and the prevalence of undetected AF is 3%. This meant that 1,434 patients would be needed in each of the two risk groups to detect a two fold difference in risk (i.e. RR of AF in high risk as compared to low risk group is 2). This RR of 2 equates to an increase in AF detection rate from 3% in the total population arm to 4% in the high risk arm. Since there was a 40:60 split in the two risk groups unequal sample size calculations only require a minimum of 1,200 patients in the high risk group and 1,800 in the moderate/low risk group. This was achievable with a screening arm of 5,000 patients, as there would actually be 1,320 in the high risk group and 1,980 in the moderate risk group if a 66% screening acceptance rate was assumed.

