### Economic analysis

#### Framework for the economic analysis

This trial evaluated a large number of alternative screening scenarios for identifying atrial fibrillation (2 screening strategies i.e. target v population; 6 screening methods i.e. pulse plus 3 types of ECG if pulse abnormal, and 3 types of ECG regardless of pulse; and 4 screening test interpretations, making 2*6*4 = 48 plus control and opportunistic screening = 50). The study has been powered to detect a difference in the targeted versus population arms, and in systematic screening versus routine clinical practice. However, the economic analysis will compare the cost-effectiveness of all alternative screening approaches using a modelling framework, whereby data will be drawn from the trial (where appropriate and available) and from external sources.

The use of a modelling approach allows the timescale for the economic analysis to be extended beyond the follow-up period allowed for in the trial. The use of such extrapolation will enable estimation of the incremental cost-effectiveness ratios (ICERs) for each approach:

Incremental cost per case detected

Incremental cost per life year gained

Incremental cost per quality-adjusted life year (QALY) gained

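### Sample size item f) equates a relative risk of 2 with a rise from 3% to 4%; on its own inputs these are different effects, and only the relative risk of 2 has 90% power

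*Protocol article*

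**What the plan says.** In the protocol article, 'Sample size and power calculations', item f) is headed: "To detect a relative risk (RR) of 2 (1% detection rate difference) between total population and high risk screening (A3 vs A2"). Its inputs follow: "It was assumed that 40% of the study population fall into the high risk group, and the prevalence of undetected AF is 3" per cent. The size is then given as "This meant that 1,434 patients would be needed in each of the two risk groups to detect a two fold difference in risk", and the relative risk is defined in brackets: "RR of AF in high risk as compared to low risk group is 2". The next sentence restates the effect: "This RR of 2 equates to an increase in AF detection rate from 3% in the total population arm to 4" per cent in the high-risk arm.

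For a 40:60 split the item asks for at least 1,200 high-risk and 1,800 moderate/low-risk patients. It expects 1,320 and 1,980 from a 5,000-patient screening arm with 66% acceptance. The same section sets the general rule: "All sample size calculations were for 90% power and 5% significance levels unless otherwise stated".

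Two other places bear on this. 'Framework for the economic analysis' says: "The study has been powered to detect a difference in the targeted versus population arms". 'Randomisation' says that high-risk and moderate-risk patients were identified by record search within the systematic screening arm.

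**The concern.** The item names its target effect in two ways, as a relative risk of 2 and as a 1-point difference (3% to 4%), and treats them as one. If they differ, the sample size can match only one of them, and the 90% power will be credited to the other without support. One point is also the difference used in items a), b), d) and e), so a reader will naturally take it as what f) can detect.

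The label is a second difficulty. The heading compares total population with high-risk screening, but the calculation compares high-risk with lower-risk patients. Both groups sit inside one randomised arm, so the economic section's mention of targeted and population arms suggests a randomised contrast that the design does not contain.

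**Working it through.** **Inputs, all from item f) and the general rule:** high-risk share 40%; overall undetected prevalence 3%; RR 2 for high against low risk; 90% power; 5% significance. Two-sided testing is assumed, since the article does not state sidedness.

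**Step 1: rates implied by RR 2.** Let p be the low-risk rate. Then 0.4 × 2p + 0.6 × p = 3%, so p = 3%/1.4 = 2.143% and the high-risk rate is 4.286%. The excess over the total is 4.286 − 3 = 1.286 points.

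**Step 2: reproduce the stated size.** The usual two-proportion formula is n = [1.960 √(2p̄(1−p̄)) + 1.282 √(p₁(1−p₁) + p₂(1−p₂))]² / (p₁ − p₂)², with p̄ the mean of the two rates.
- At 2.143% and 4.286%: (0.4889 + 0.3191)² / 0.02143² ≈ 1,422 per group. The article gives 1,434.
- At 40:60: 1,168 high-risk and 1,752 low-risk. The article gives 1,200 and 1,800.
- 5,000 × 0.66 = 3,300, split 40:60, gives 1,320 and 1,980 exactly.

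The published figures therefore come, within about 3%, from the unrounded RR 2 rates. The 4% appears not to have entered the calculation.

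**Step 3: rates implied by 3% to 4%.** Low-risk rate = (3% − 0.4 × 4%)/0.6 = 2.333%; RR = 4/2.333 = 1.71. The same formula gives (0.4854 + 0.3170)² / 0.01667² ≈ 2,318 per group (about 2,436 with continuity correction). At 40:60 without correction it is 1,910 and 2,865.

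**Step 4: power with 1,320 high-risk and 1,980 lower-risk attenders.** z = (difference − 1.960 × SE₀)/SE₁, where SE₀ uses the pooled rate and SE₁ the separate rates. The continuity correction takes ½(1/1,320 + 1/1,980) = 0.0006 off the difference.

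| Effect | Rates, high v low | RR | z (uncorrected) | Power | With continuity correction |
|---|---|---|---|---|---|
| RR 2, 3% overall | 4.29% v 2.14% | 2.00 | (0.02143 − 0.01188)/0.00645 = 1.48 | 93% | 92% |
| 3% to 4% | 4.00% v 2.33% | 1.71 | (0.01667 − 0.01188)/0.00637 = 0.75 | 77% | 74% |
| 2% to 3% | 3.00% v 1.33% | 2.25 | (0.01667 − 0.00975)/0.00536 = 1.29 | 90% | 88% |

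The last row uses the changes that the opening assumptions of the same section expect: about 2% for the whole systematic arm and about 3% for its high-risk part. The low-risk rate is (2% − 0.4 × 3%)/0.6 = 1.33%. At the stated minimum of 1,200 and 1,800, uncorrected power is 91% for RR 2 and 74% for 3% to 4%.

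**Step 5: does high against low risk address high risk against total?** Since the total rate is 0.4 p_high + 0.6 p_low, p_high − p_total = 0.6 (p_high − p_low). Check: 0.6 × 2.143 = 1.286 and 0.6 × 1.667 = 1.000. With the risk-group shares taken as fixed, one difference is zero exactly when the other is, and a test of either has the same power.

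**The case against.** The strongest reply is that nothing in the design is wrong. The article names a twofold risk as its target more than once, the patient numbers fit that target, and the expected attenders exceed it. The 4% can be read as 4.29% rounded to a whole per cent, and 1 point as 1.29 rounded likewise. At the detection rates expected elsewhere in the same section (2% and 3%), a 1-point gap has about 88–90% power.

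Most of this stands. It rules out three stronger readings that a reader might infer:

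- *That 1,434 is miscalculated, or the study too small for f).* Step 2 reproduces it for RR 2. The 2,318 is the requirement for a smaller effect, not a correction of the stated figure.
- *That f) tests two nested groups as if they were independent.* Only the heading's label is nested. The groups actually sized are disjoint, and by Step 5 the comparison does speak to yield per person screened in high-risk against total screening.
- *That the economic comparison of targeted and population screening rests on power the study lacks.* The sentence after the power claim says that the economic analysis compares all approaches by modelling. Incremental cost per case detected, a primary outcome, already counts the cases that targeting misses.

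Rounding does not dispose of the remainder. The text says that RR 2 equates to 3% to 4%, the heading gives 1% as the detectable difference, and 90% power is claimed throughout. From a base of 3%, taking 1.29 points as 1 lowers power from 93% to 77%.

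**Conclusion.** The concern holds as an error in the stated effect and in the power attached to it, together with inexact labels. On the article's own inputs, RR 2 is 1.29 points above the total, not 1. A rise from 3% to 4% is RR 1.71 and has about 77% power at the expected attendance (74% with continuity correction), not 90%.

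The shortfall is specific to a 3% base: a 1-point gap from 2% to 3% is powered at about 88–90%. The figures assume a two-sided 5% test, a 40:60 split, 66% acceptance, and the same underlying rates in attenders as in the whole arm. The sample size for RR 2 and the trial design are unaffected. What f) powers is a non-randomised difference in yield between two risk groups within one arm.

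**What to change.** 1. In item f), restate the comparison as high-risk against moderate/low-risk attenders within the systematic arm, not randomised. Give 90% power for RR 2 (4.3% against 2.1%, 1.3 points above the total), about 74–77% for 3% to 4% (RR 1.71), and about 88–90% for 2% to 3% (RR 2.25), each with its base rate.
2. Replace the heading's A3 against A2 label and its 1% gloss accordingly.
3. In 'Framework for the economic analysis', replace the claim about targeted and population arms with a statement that the study is powered for a difference in yield between risk groups within the systematic arm.

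Optionally, report the share of screen-detected cases found in the moderate-risk group with its 95% confidence interval. On the article's inputs the expected cases are 1,320 × 4.286% = 56.6 and 1,980 × 2.143% = 42.4, 99 in all. The share is 43%, with standard error √(0.43 × 0.57/99) = 0.050, so about ±10 points. This would show directly how much targeting misses.

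The cost is rewording, plus one proportion from data already collected if the option is taken. No patients are added. The price is a less favourable stated power for the rise from 3% to 4%.

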### Sample size for quality of life assessment

Although some of the variances are from North American populations we have no reason to suspect that the variation will be different in a British population since data from the ECHOES study on the SF36 gives variations very similar to the North American norms.

### Spielberger

The shortened (6-item) version of the Spielberger state anxiety questionnaire has been validated and used in populations different from that under consideration in SAFE, namely it tends to have been used in young and mostly female populations [17,21,22]. The variance obtained from these papers appears to be approximately 144 for Marteau [17] but higher for the Ubhi [22] paper. However, the women in the latter paper were being informed of major illness outcomes (either benign or malignant breast cancer). A full Spielberger on people undergoing physiological tests also gave a variance of the order of 144 [23]. The full version of the Spielberger state anxiety when used with an elderly population also seems to give a variance that is not too far from the previously mentioned papers being 188.8 [23]. Taking this latter value as being the nearest to our population we can detect a 4 point difference in the mean values obtained with 249 patients in each arm.

### EQ5D

#### The VAS scale

The VAS variance as reported for an elderly population aged 75 and over was 365 [24] but for a group of recovered stroke patients (ages not given) it was approximately 100 [25]. Taking the former value as a worst case this means it will be possible to detect a 6% difference between groups on the VAS with 213 patients within each group.

#### The Utility index

This was reported in different ways in the Johnson [24] and Dorman [25] papers. Using the utility values from the Dorman et al paper the variance is approximately 0.066 and this allows us to detect a 0.1 difference with 139. Using the Johnson paper the variance is approximately 576 and using this means that we can detect a mean change of 7 with 247 patients in each arm.

### Statistical analysis

Intention to treat analysis will be used.

Any previously known Atrial Fibrillation cases will be subtracted from the totals obtained at the end of the study to ensure there is no double counting in the incidence figures.

Chi-squared, independent t-tests and log-linear models will be used to describe demographic data. If there are differences between the groups this may need to be adjusted for in later analyses.

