#### Targeted screening

One possible approach was to screen patients who are at higher risk of AF – a *targeted screening programme*. Cardiac failure, hypertension and rheumatic heart disease are important precursors of AF [7]. AF is more common in people with a history of myocardial infarction, angina, diabetes mellitus, hyperthyroidism, stroke or transient ischaemic attack (than in people without these conditions) [11]. Most general practices were computerised, and some have disease registers. A targeted screening programme could exploit these to identify such high risk patients, either through disease registers, or through prescribing information on the computerised records.

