### Primary objective: to determine baseline prevalence and incidence of AF on a variety of screening strategies

Proportions and rates will be used as the measures of prevalence and incidence.

The independent t-test and ANOVA with random effects (as appropriate) will be used to examine the detection rate differences between the intervention and control screening strategies. Should the data be strongly non-normal a non-parametric equivalent will be used.

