#### Randomisation

Randomisation of practices and patients was performed by statisticians from the Department of Primary Care and General Practice at The University of Birmingham. Cluster randomisation of practices to intervention or control was stratified by Townsend quartiles and practice size. Computer searches were carried out to identify cases of known AF, within the sample of patients identified above, using a published strategy [15]. The randomisation of patients within the intervention practices ensured that the study patients in each practice were divided equally between systematic and opportunistic screening arms and also that there was an even distribution of patients with known AF between the two arms. Patients within the systematic screening arm were identified by computerised record searching as either being at high risk (target population) or moderate risk (non-target population) of AF by recognised criteria [28,11].

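### Covariate adjustment is left to depend on observed baseline differences, and the factors used to stratify practices are not carried into the analysis

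*Protocol article*

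**What the plan says.** The Statistical analysis section opens its treatment of baseline data with "Chi-squared, independent t-tests and log-linear models will be used to describe demographic data" and continues directly with "If there are differences between the groups this may need to be adjusted for in later analyses". It gives no covariate, no criterion for a difference and no unit of analysis for these tests.

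The section on the primary objective states: "The independent t-test and ANOVA with random effects (as appropriate) will be used to examine the detection rate differences". Random effects are provided for there, as appropriate, but no covariate or stratification factor is named.

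The Randomisation section states: "Cluster randomisation of practices to intervention or control was stratified by Townsend quartiles and practice size". Within intervention practices, patients were then split equally between systematic and opportunistic screening, with the further condition "also that there was an even distribution of patients with known AF between the two arms". No section says that the practice strata enter any model.

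The Sample size section shows that the authors allowed for clustering in the main comparisons. It gives a between-practice variance of 3.7, a within-practice variance of 246, an ICC of 0.015, clusters of 200 and a design factor of 4. It also says that comparisons a), b) and c) are at practice level.

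**The concern.** There are three difficulties, of unequal weight.

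1. A baseline difference between randomised groups is a chance event. Its size or p-value does not tell the analyst whether the variable predicts AF detection, and that is the only good reason to adjust for it. The article already identifies predictors without any test, for example: "Cardiac failure, hypertension and rheumatic heart disease are important precursors of AF". Choosing covariates from observed imbalance leaves the form of the primary model open until the data have been seen.

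2. The practices were randomised within strata. An analysis that leaves the strata out gives up whatever precision the stratification bought, to the extent that deprivation and list size predict detection.

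3. Chi-squared and independent t-tests in their ordinary form treat patients as independent. Applied in that form to intervention versus control practices, they would report far more differences than their nominal level suggests, and each could prompt an adjustment.

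At stake is whether the main comparison can be shown to have been fixed in advance, and how precise it is.

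**Working it through.** **Step 1. Reproduce the plan's clustering figures (Sample size section).**
- ICC = 3.7 / (3.7 + 246) = 0.0148, stated as 0.015.
- Design factor = 1 + (200 − 1) × 0.015 = 3.985, stated as 4.
- For "To detect a 1% difference in detection rate between intervention (GP educated) and control practices", 1% against 0% with 90% power, 5% two-sided and a continuity correction gives 1,236 patients, as stated. The document does not state sidedness; the two-sided version is the one that reproduces.
- 1,236 × 4 = 4,944, rounded in the plan to 5,000 per group.

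**Step 2. How often a patient-level baseline test would flag a chance difference, intervention versus control.** If the true variance is DE times what the test assumes, a nominal 5% test rejects with probability 2 × (1 − Φ(1.96/√DE)). With DE = 4 this is 2 × (1 − Φ(0.98)) = 0.327; with DE = 3.985 it is 0.326.

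A simulation with 25 practices of 200 patients per arm, no true difference and ICC 0.015 gave 33% for the patient-level test and about 5% for a t-test on practice proportions.

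The ICC of 0.015 is for AF. The article gives none for a demographic variable, so a range is assumed:

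| Assumed ICC | DE (200 per practice) | Flagged at nominal 5% |
|---|---|---|
| 0.001 | 1.199 | 7% |
| 0.005 | 1.995 | 17% |
| 0.01 | 2.99 | 26% |
| 0.015 | 3.985 | 33% |
| 0.03 | 6.97 | 46% |

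If all 10,000 intervention patients (400 per practice) are compared with the 5,000 controls at ICC 0.015, the combined factor is (2 × 3.985 + 6.985)/3 = 4.985, and the test flags 38% of the time.

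**Step 3. What this does to the primary test.** The rates in Step 2 concern baseline tests, not the trial's conclusion. To see the effect on the conclusion, take 25 versus 25 practices, no treatment effect, and one practice-level covariate with an assumed correlation with the outcome. Adjust only when the patient-level baseline test flags (DE 4). Simulated type I error of the primary comparison:

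| Assumed correlation | Adjust only if flagged | Adjust always |
|---|---|---|
| 0.2 | about 4.8% | 5% |
| 0.5 | about 3.7% | 5% |
| 0.7 | about 2.6% | 5% |

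The rule is conservative: it removes large chance imbalances and leaves the others in an unadjusted standard error.

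**Step 4. Precision.** A covariate with correlation r leaves a fraction √(1 − r²) of the standard error when always adjusted for: 0.98 at r = 0.2, 0.87 at 0.5, 0.71 at 0.7. The article does not say how strongly Townsend quartile or practice size predicts detection, so the actual gain is unknown.

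**The case against.** The strongest reply is that a rule is being read into loose wording. The tests are said to describe the data, and adjustment only may be needed. No significance threshold is written, and the section does not say whether patients or practice summaries are tested. That is fair: both the significance trigger and patient-level testing are inferred from the tests named. What is not inferred is that adjustment is made conditional on observed differences. Without a criterion, the choice is even more open.

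A second reply is that the covariate list commonly belongs in an SAP or full protocol, neither of which is shown. As a complaint about a missing list, the point would fail. But the article states a conditional approach, and a later plan could fix the covariates only by replacing that sentence.

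Four stronger readings are tempting, and the document does not support them:
- *The trial's false-positive rate is 33%.* That figure is how often a baseline test would flag. Step 3 shows a conservative primary test under a mechanical rule. It does not examine free choice among many covariates, so inflation is neither shown nor excluded there.
- *Known AF is left out of the analysis.* Known cases are subtracted, the comparisons are defined as changes from baseline known prevalence, and known AF was balanced between the patient-level arms.
- *The clustering figure covers every comparison.* Systematic and opportunistic patients were randomised within practice, so practice effects largely cancel.
- *A given number of variables would be flagged.* The article does not say how many would be tested.

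**Conclusion.** The point holds in limited form. The protocol article ties adjustment to baseline differences seen after chi-squared and t-tests and does not carry its own practice strata into the analysis. A fixed adjustment is better and costs almost nothing.

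The flagging rate of about 33% in the practice-level comparison assumes patient-level tests and the AF design factor. With the assumed ICC range it is 7% to 46%, above 5% throughout. The consequences are a data-driven primary model, some loss of precision of unknown size and, for a mechanical one-covariate rule, a type I error of about 2.6% to 4.8% for assumed correlations of 0.7 down to 0.2. This is not evidence that the trial would claim effects that do not exist. For systematic versus opportunistic screening only the objection to data-dependent adjustment applies.

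**What to change.** Replace the conditional sentence with an adjustment fixed in advance:

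- **Intervention versus control:** models that account for practice and always include Townsend quartile, practice-size stratum and age. Add sex if it is held for control patients. The article records sex only at the screening clinic, which is not part of the control arm, so availability must be confirmed first.
- **Systematic versus opportunistic:** practice as a block.
- **Baseline data:** summaries by group, without hypothesis tests.

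Baseline known AF already enters through the subtraction and the change-from-baseline definitions, so using it as a covariate as well is optional.

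The change is to analysis wording; sample size is unaffected. The price is a few degrees of freedom among 50 practices. A practice-level two-group comparison has 48, Townsend quartile takes 3, and practice size takes one fewer than its number of strata, which the article does not give. The Discussion says a draft report has already been submitted, so if conditional adjustment was used there, the fixed model can be reported beside it.
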